#### Structured telephone interview and baseline assessment (T0)

2.4.2

Potentially eligible participants will be contacted by telephone to schedule a video call interview with a clinical psychologist. At the beginning of the video call, women will access a web-based informed consent for participating in the study. The interview will collect sociodemographic and clinical history information and assess for eligibility. The Mini-International Neuropsychiatric Interview (MINI: Sheehan et al., 1998; Ferrando et al., 2000) will be used to assess minor and major depression diagnosis and mental health exclusion criteria. After the interview and during the video call, women satisfying the eligibility criteria will access a web link to complete the baseline questionnaires online.

### Participant safety

2.5

A standardized operating procedure will be followed in case individuals are defined as showing a moderate or severe risk for suicide. During the initial screening and eligibility assessment, individuals with moderate or severe suicidal ideation will be excluded from the study. They will be asked to discuss their symptoms with a general practitioner or mental health specialist as soon as possible. Additionally, they will receive detailed information about the national program for the treatment of depression and emergency contact numbers. After randomization, during other assessment points, women with >1 point in question 9 of PHQ-9 or >1 point in question 10 of the EPDS (“The thought of harming myself has occurred to me”; response options Yes, quite often (3), Sometimes (2), Hardly ever (1) and Never (0)) will be contacted by telephone. They will receive the same information mentioned above. A similar procedure will be followed if participants included in the trial show symptoms of suicidality throughout the study phase (i.e., by mentioning symptoms of suicidality when contacting the e-coach or when the content of their homework exercises hints at potential suicidal ideation). In such a case, the participant's suicidality risk will be assessed with the suicidality module of the MINI Interview. Participants presenting moderate or severe suicidal ideation will be referred to mental health care, and their suicidal risk will be monitored regularly throughout the study.

### Randomization

2.6

Women who meet inclusion criteria will be randomized to “*Mamá, te entiendo*” or WL. An independent person not involved in the study will generate the allocation sequence. Stratified randomization will be conducted according to depressive symptom severity (minor or major depression). To generate the random allocation sequence, we will use the software Study Randomizer (2017) using permuted block randomization with block size of 6 in a 1:1 ratio. Researchers will be blind to the randomization process and will be notified through email regarding participant allocation by an independent researcher. Once randomized, participants and research personnel will not be blinded to group condition, except for T1 and T2 interviewers. Following the notification, participants will be contacted by email to inform them of their assigned group (i.e., intervention or WL). The intervention group will receive instructions for registering into the app.

### Intervention condition: “*Mamá, te entiendo*” (“*Mom, I get you*”)

2.7

Participants in this condition will receive a guided internet-based, cognitive-behavioral, 8-week intervention for postpartum depression symptoms. It also includes elements from attachment and mentalization theories. *“Mamá, te entiendo”* is a web app, a type of app that can be accessed through a web browser. It was developed based on the CeHRes Roadmap (van Gemert-Pijnen et al., 2011) through a participatory process that involved continuous evaluation cycles. Ten focus groups were conducted with perinatal women and healthcare professionals, and five usability interviews with potential end users. Additionally, a pilot with ten postpartum women was conducted to assess the app's proper functioning. The development process will be published elsewhere.

*“Mamá, te entiendo”* consists of the following sections:

#### Main and optional modules

2.7.1

The intervention consists of six main sequential modules and three optional modules. The main modules address the following: Psychoeducation on depression, How the cognitive-behavioral approach works, Identifying thinking errors, Cognitive restructuring, Problem-solving, and Behavioral activation. The optional modules address: Psychoeducation on anxiety, Exposure strategies, and Communicational Skills. Five case examples of mothers illustrate depressive symptoms and techniques. There is also an introductory module describing the app's functioning (without therapeutic content), and a guide about maintaining changes is displayed when the last main module is completed.

#### Homework exercises (Workbook)

2.7.2

All modules except the two psychoeducational ones include homework. All homework exercises can be accessed through a specific section in the app called “Workbook”. Participants will receive feedback from an e-coach through the app. They also can contact the e-coach to solve doubts about the app content and exercises. The e-coaches will be psychologists, Ph.D. in Psychotherapy candidates, with a Master's degree in clinical psychology, and training in perinatal mental health. The e-coaching protocol of the Caring Universities Project was adapted for this intervention.

#### Infographics

2.7.3

Another section of the app includes infographics about other relevant topics: 1) Guide to healing, 2) How to strengthen the support network, 3) Postpartum rage, 4) The postpartum body, 5) Dealing with doubts/comparison/over information, 6) Mentalizing my baby, 7) The couple's relationship in the postpartum period, 8) Returning to work after the maternity leave.

#### Reading for the support network

2.7.4

A shareable document with reading about how to support a loved one struggling with depression symptoms is included.

#### Favorites section

2.7.5

Women can tick any part of the content as “add to favorites” and save it in a “Favorites” section.

#### Resources section

2.7.6

A resources section includes links to websites, hotlines, and documents of interest.

#### Other sections

2.7.7

The app includes a section presenting the team that contributed to the app's development and the content references. There is a contact section where participants can send a message to the Information and Technology support team to notify them about technical issues if they appear.

Participants are instructed to add a shortcut to “*Mamá, te entiendo*” web app to their smartphone home screen after registration.

### WL condition

2.8

Participants in the WL condition will receive the same assessments as those in the intervention condition. Participants allocated to WL may access their local mental health services during their waiting period. After the follow-up assessment, the WL group will be offered access to the intervention.

### Outcome assessments

2.9

#### Primary outcomes: feasibility and acceptability

2.9.1

Feasibility and acceptability outcomes of interest relate to methodological, procedural, and clinical uncertainties. They will examine recruitment and eligibility; data collection; attrition; participants' intervention adherence, use, and acceptability; and resources needed to complete the study and intervention. Table 1 shows more detail on the feasibility and acceptability outcomes. Intervention credibility and expectancy of benefit will be assessed at baseline by the CEQ-6 (Devilly and Borkovec, 2000), and satisfaction with the intervention will be evaluated post-intervention by the CSQ-8 (Attkisson and Greenfield, 1994; Vázquez et al., 2019). A sub-sample of participants will be selected and invited to participate in a qualitative evaluation to gain more insight into participants' perspectives on the intervention and study procedures.

**Table 1 t0005:** Overview of feasibility and acceptability outcomes.

Outcome	Evaluation
Recruitment and eligibility	Number assessed for eligibility by the initial screening
	The proportion of potentially eligible participants from the initial screening
	Number contacted for the eligibility interview
	Number evaluated for eligibility by the eligibility interview
	The proportion fulfilling inclusion criteria (eligibility rate)
	The proportion diagnosed with minor depression
	The proportion diagnosed with major depression
	Reasons for ineligibility
Participants' expectations	Intervention credibility and expectancy of benefit (CEQ-6)
Data collection	Percentage completing assessments at the different time points
Attrition	Rates of study dropout
	Rates of intervention dropout
Participants' adherence to the intervention	Percentage of participants who completed all main modules
	Average, range, and standard deviation of the number of main modules completed
	Average, range, and standard deviation of the number of modules completed
	Average, range, and standard deviation of homework exercises sent to the e-coach
Participants' acceptability of intervention and data collection, and exploration of mechanisms of impact	Satisfaction with the intervention (CSQ-8)
	Engagement with the intervention (TWEETS)
	Impressions and experiences of working with the intervention (positive and negative) and of completing questionnaires and interviews (with a subsample; qualitative)
	Views concerning the impact of the intervention and its different features on their mood
	Reasons for poor attendance and withdrawal (with a subsample; qualitative)
Resources needed to complete the study and the intervention	Length of time required for: ‐ Participants to complete questionnaires and interviews ‐ e-coaches to deliver the intervention ‐ Study personnel to administer the study

CEQ-6: Credibility and Expectancy Questionnaire-6; CSQ-8: Client Satisfaction Questionnaire-8; TWEETS: TWente Engagement with Ehealth Technologies Scale.

##### Credibility expectancy questionnaire (CEQ-6)

2.9.1.1

The CEQ (Devilly and Borkovec, 2000) is a 6-item self-report questionnaire that measures treatment credibility, defined as “how believable, convincing, and logical the treatment is” and expectancy, defined as “improvements the client believes will be achieved”. The CEQ has good internal consistency and good test-retest reliability (Devilly and Borkovec, 2000).

##### Client satisfaction questionnaire (CSQ-8)

2.9.1.2

The CSQ-8 (Attkisson and Greenfield, 1994) is an 8-item self-report questionnaire that assesses the general level of satisfaction with a service received. The Spanish version of the CSQ-8 has adequate psychometric properties and maintains those of the original questionnaire (Vázquez et al., 2019).

##### TWente engagement with Ehealth technologies scale (TWEETS)

2.9.1.3

The TWEETS (Kelders et al., 2020) is a 9-item self-report measure that assesses engagement with an eHealth technology. Of the nine items, three are aimed at assessing behavioral engagement, three at cognitive engagement, and three at affective engagement. Each item is measured on a 5-point Likert scale ranging from “strongly disagree” to “strongly agree”. The TWEETS performs well as an engagement measure with high internal consistency, reasonable test-retest reliability and convergent validity, good divergent validity, and reasonable predictive validity (Kelders et al., 2020). A forward-backward translation process was conducted to produce a Spanish version for this study.

##### Qualitative process evaluation

2.9.1.4

After the follow-up assessment, a sub-sample of participants from the intervention group will be invited to participate in semi-structured interviews. These participants will be selected through non-randomized propositive sampling according to participants' adherence (high and low), and the sample size cannot be stated a priori. High adherent participants will be defined as completing at least four main modules, and low adherence will be defined as completing less than three. However, these criteria may be adjusted later according to the data. The interviews will explore positive and negative impressions and general experiences with the intervention and study procedures. In addition, to examine possible mechanisms of change in highly adherent participants, their views concerning the impact of the intervention and its different features on their mood and lives more generally will be explored. Interviews with poor adherent participants will explore reasons for disengaging and barriers to treatment and examine suggestions for future intervention development and study procedures.

#### Secondary outcomes

2.9.2

The secondary outcomes of this study are depression, perceived social support, mother-infant bonding, maternal satisfaction and self-efficacy, and mental health care services use.

##### Mini-international neuropsychiatric interview (MINI)

2.9.2.1

The MINI (Sheehan et al., 1998; Ferrando et al., 2000) explores 17 mental disorders defined in the DSM-IV-R (axis I), focusing on current symptomatology. This study will use the MINI to assess eligibility and as an outcome measure. It will also evaluate the presence of generalized anxiety disorder. At T1 and T2, only the major depressive episode section will be used. The Spanish version of this instrument has shown acceptable sensitivity and specificity for the most prevalent psychiatric disorder diagnosis (Bobes, 1998). Its psychometric properties have not been studied in the Chilean population, but it has been used in perinatal mental health research (Olhaberry et al., 2015; Rojas et al., 2007). The MINI interviewers will be clinical psychologists and will be masked for the condition.

##### Patient health questionnaire -9 (PHQ-9)

2.9.2.2

The PHQ-9 (Kroenke et al., 2001; Diez-Quevedo et al., 2001) is a 9-item self-report measure of depressive symptoms experienced over the past two weeks. The PHQ-9 is based on the Diagnostic Statistical Manual, fourth edition (DSM-IV: APA, 2000) diagnostic criteria for major depressive disorder. Participants rate the frequency of symptoms (e.g., ‘Feeling down, depressed, or hopeless’) on a 4-point scale ranging from “not at all” to “nearly every day”. Total scores range from 0 (no symptoms) to 27 (severe). Scores >9 are indicative of a clinically significant level of depressive symptoms. The measure has good psychometric properties (Kroenke et al., 2001) and has been validated in postpartum samples (Gjerdingen et al., 2009). The Spanish version (Diez-Quevedo et al., 2001) has been validated in Chile, showing good psychometric properties (Baader et al., 2012; Saldivia et al., 2019).

##### Edinburgh postpartum depression scale (EPDS)

2.9.2.3

The EPDS (Cox et al., 1987) consists of ten multiple-choice questions on a 4-point scale ranging from 0 to 3 according to the severity of the symptoms. The total score goes from 0 (no symptoms) to 30 (severe symptoms). It has been validated in various countries and cultures, including Chile (Jadresic et al., 1995). Higher scores indicate more significant depressive symptoms, and three categories of depressive symptomatology are identified: no risk, probable risk, and probable depression.

##### Multidimensional scale of perceived social support (MSPSS)

2.9.2.4

The MSPSS (Zimet et al., 1988) is a 12-item measure of perceived adequacy of social support from three sources: family, friends, & significant other. It was translated and validated in Chile (Arechabala Mantuliz and Miranda Castillo, 2002). In the Chilean version, the questions are rated on a 4-point scale ranging from “rarely” to “always”.

##### Postpartum bonding questionnaire (PBQ)

2.9.2.5

The PBQ (Brockington et al., 2006) is a 25-item self-report measure that assesses mother-infant bonding through the mother's feelings and attitudes toward her infant. The questions are rated on a 6-point Likert scale ranging from “not at all” to “always”. A validated Spanish version of the PBQ will be used in this study (Garcia-Esteve et al., 2016).

##### Escala de Evaluación parental [parental assessment scale] (EEP)

2.9.2.6

The EEP (Farkas-Klein, 2008) is a 10-item self-report measure that assesses satisfaction and self-efficacy regarding motherhood in women with children between 0 and 2 years of age. Each item is measured on a 10-point Likert-type scale, ranging from “totally Disagree” to “totally agree”. The scale was developed and validated in Chile, showing good psychometric properties.

##### Mental healthcare services use

2.9.2.7

Data on mental healthcare services use (presence/absence, frequency, and duration) will be collected.

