#### Sociodemographic and clinical history variables

2.9.3

Data on age, education, socioeconomic status, employment status, relationship status, ethnicity, nationality, number of children, number of people who comprised the family unit, pregnancy planning, pregnancy complications, baby's date of birth, mother and baby current health problems, prior and current psychological and psychiatric treatment (diagnosis, treatment type, and duration) and the presence of early experiences of sexual abuse and violence will be collected at the eligibility interview. Data on employment and relationship status will be updated at post-intervention and follow-up.

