### Data collection and management

2.10

All data will be collected online via video call (interviews) or web platform (self-report questionnaires). Participants' data that can be directly traced to them (names, email addresses, and telephone numbers) will be coded to protect their privacy. Non-coded data will be saved separately, and only the principal researcher will have access to this data file. Self-report data will be collected using a secured online-based assessment system. All measurements collected during the study with their time points are shown in Table 2. An email account was created for the study to send participants allocation. Only the principal researcher will have access to the study email account. Semi-structured acceptability interviews will be recorded and transcribed. The transcriptions will have no personal data, and the recordings will be deleted after transcription.

**Table 2 t0010:** Overview of measures and assessment points.

Variable	Measure	Assessment points		
		T0	T1	T2
Sociodemographic and clinical history variables	Structured questions	x	Update on employment situation & relationship status	Update on employment situation & relationship status
Diagnostic interview	MINI	x	Only depression section	Only depression section
Intervention credibility and expectancy of benefit	CEQ-6	x		
Depression	PHQ-9	x	x	x
Postpartum depression	EPDS	x	x	x
Social support	MSPSS	x		x
Mother-infant bonding	PBS	x		x
Maternal satisfaction and self-efficacy	EEP	x		x
Engagement with the technology	TWEETS		x	
Satisfaction with the intervention	CSQ-8		x	

T0 = pre-treatment (baseline).

T1 = post-intervention (8 weeks after randomization).

T2 = follow-up (12 weeks after randomization).

MINI: Mini-International Neuropsychiatric Interview.

CEQ-6: Credibility and Expectancy Questionnaire-6.

PHQ-9: Patient Health Questionnaire-9.

EPDS: Edinburgh Postnatal Depression Scale.

MSPSS: Multidimensional Scale of Perceived Social Support.

PBS: Postnatal Bonding Scale.

EEP: Escala de Evaluación Parental.

TWEETS: TWente Engagement with Ehealth Technologies Scale.

CSQ-8: Client Satisfaction Questionnaire-8.

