### Analyses

2.11

Statistical analysis of feasibility indicators is described in Table 1. The qualitative data from the interviews will be analyzed by two independent coders using thematic content analysis (Braun and Clarke, 2006). Themes will be identified, described, and subsequently categorized. Descriptive statistics will be reported, including the means and standard deviations (SDs) or medians and interquartile ranges for each questionnaire at T0, T1, and T2.

For preliminary efficacy on depressive symptomatology reduction, data will be analyzed following CONSORT guidelines; between-group comparisons will be by intention-to-treat. Missing data will be imputed using the Markov Chain Monte Carlo (MCMC) multivariate imputation algorithm. Comparison between groups will use repeated measures analysis of covariance (ANCOVA) with adjustment for baseline in a random-effects model. Interaction between time and group will be assessed (for changes in group effects with time). In the absence of such an interaction, the overall difference between groups across the two follow-up assessments will be calculated (95 % CIs and *p* values). Secondary analyses will include an adjustment for baseline characteristics. Other secondary outcomes will be analyzed with the same procedures.

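### Mental healthcare services use is a named secondary outcome, but the assessment schedule gives it no time point and the itemised T1 and T2 updates leave it out

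*Protocol article*

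**What the plan says.** Four parts of the protocol article bear on this.

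- **Outcome list (2.9.2 and 2.9.2.7).** "The secondary outcomes of this study are depression, perceived social support, mother-infant bonding, maternal satisfaction and self-efficacy, and mental health care services use". The subsection on the last of these says only that "Data on mental healthcare services use (presence/absence, frequency, and duration) will be collected". It names no assessment point.
- **Schedule (2.10, Table 2).** "All measurements collected during the study with their time points are shown in Table 2". Table 2 has no row for services use.
- **Clinical history (2.9.3).** Past and present psychological and psychiatric treatment is taken at the eligibility interview. For later visits the section says "Data on employment and relationship status will be updated at post-intervention and follow-up", and the T1 and T2 cells of Table 2 repeat this: "Update on employment situation & relationship status".
- **Comparator and analysis (2.8, 2.11).** "Participants allocated to WL may access their local mental health services during their waiting period". Depression is analysed by repeated-measures ANCOVA adjusted for baseline in a random-effects model, and "Other secondary outcomes will be analyzed with the same procedures".

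**The concern.** An outcome that is to be compared between arms after randomisation needs at least one measurement after randomisation. The schedule gives this one none, and the list of what is refreshed at T1 and T2 is specific enough to exclude it. Site staff and the builders of the web questionnaires work from the schedule, so a missing row can become missing data. Care received between randomisation and week 12 is hard to reconstruct later.

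The article itself gives reasons to expect outside care:

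- Waitlist women may seek it (2.8).
- Women with moderate or severe screening scores are encouraged to discuss their symptoms with a doctor or specialist (2.4.1), and many of them remain potentially eligible.
- Participants found at moderate or severe suicide risk during the study are referred to mental health care, with no restriction by arm (2.5).
- The Background says that patients whom a general practitioner diagnoses with depression are guaranteed low-cost or free treatment.

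At stake are the trial's ability to report one of its own outcomes and a description of what the waitlist arm actually received. The second is the kind of information that a feasibility trial is meant to hand to the definitive one.

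**Working it through.** There is no stated figure to reproduce, because the point is about the schedule. The check sets each subsection of 2.9.2 against Table 2.

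| Secondary-outcome measure | T0 | T1 | T2 |
|---|---|---|---|
| MINI | yes | depression section | depression section |
| PHQ-9 | yes | yes | yes |
| EPDS | yes | yes | yes |
| MSPSS | yes | – | yes |
| Bonding (PBQ in 2.9.2.5, PBS in Table 2) | yes | – | yes |
| EEP | yes | – | yes |
| Mental healthcare services use | – | – | – |

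1. **Coverage.** Six of the seven measures have at least one post-baseline point. Services use has 0 of 3 points.
2. **Could another row carry it?** The only candidate is the row of structured sociodemographic and clinical history questions. Its T1 and T2 cells name two items, neither of them treatment or service use, and 2.9.3 names the same two.
3. **Is baseline covered?** Partly. The history item in 2.9.3 asks for diagnosis, treatment type and duration. It does not ask for frequency, which 2.9.2.7 requires.
4. **Can the planned analysis run?** Section 2.11 applies the baseline-adjusted repeated-measures procedure to the other secondary outcomes. Its response values are the post-baseline ones, and the schedule supplies none for services use. No between-arm comparison could be formed.

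**Scale, for illustration only.** Suppose uptake of outside care in the waitlist exceeds that in the app arm by 0 to 40 percentage points, and that such care is worth 0.5 SD. Both figures are assumptions. The depression difference would then be reduced by 0 × 0.5 = 0 to 0.40 × 0.5 = 0.20 SD. For comparison, take 33 women per arm (2.3) and the pooled effect of 0.64 cited in the Background. The standard error of the standardised difference is √(2/33 + 0.64²/(2 × 66)) = √(0.0606 + 0.0031) ≈ 0.25, and the 95% half-width is about 0.49. Even the upper end of the assumed range lies inside this trial's own uncertainty.

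**The case against.** The strongest reply is that the data are plainly meant to be collected and a table row was dropped. Section 2.9.2.7 commits to collection. It asks for frequency, so it is not just the baseline history item repeated. The analysis section presupposes follow-up values. Table 2 is also loosely edited: it omits module and homework counts, time and resource measures and the qualitative interviews, and its name for the bonding scale differs from the text. Fig. 1, described as an overview of assessment points, is not available here and may show the item.

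Much of this stands. A reader might infer that care after randomisation will never be recorded, and the documents do not support that. They show a stated intention and a schedule that contradicts it. The contradiction remains, however. Module counts and resource times need no question put to the woman at T1 or T2, whereas the article names no source for services use other than collection from participants. If Fig. 1 does list the item, Table 2 and 2.9.3 would still disagree with it.

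A reader might also infer that the depression difference becomes uninterpretable. It does not. By intention to treat, the contrast is the app against a waitlist that is free to seek care, so outside care is part of the comparator. Missing services data limit the explanation of the result and leave its validity intact.

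Nor can it be said that the definitive trial's sample size would be wrong by a known factor. Any such factor rests on assumed uptake and effect. If the next trial keeps the same comparator, the effect observed against that comparator is the relevant one.

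**Conclusion.** The point holds as an internal contradiction. Sections 2.9.2, 2.9.2.7 and 2.11 treat services use as an outcome to be measured and compared, while Table 2 and the itemised updates in 2.9.3 provide no assessment point for it. This is more than detail left to a fuller document, because the article offers a schedule that it calls complete and lists what is updated, and both leave the outcome out.

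The consequence is confined to one secondary outcome and to the description of the comparator. The feasibility and acceptability outcomes are untouched, and the efficacy analysis is preliminary in any case. The conclusion needs no numerical assumption. It rests on the text of Table 2 and 2.9.3 as shown, with Fig. 1 unseen. The article mentions outside care as permitted only for the waitlist and gives no such statement for the app arm, which is a reason to measure it in both. This is a worthwhile correction of moderate weight, easiest to make before recruitment opens.

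**What to change.** - Add a row to Table 2 for mental healthcare services use at T0, T1 and T2 in both arms, covering presence, frequency and duration. At T1 and T2 the recall period should be the time since the last assessment.
- Align 2.9.3 with that row, so that its list of post-baseline updates no longer leaves treatment out, and check that Fig. 1 agrees.
- Report services use by arm next to the depression results.

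Putting the items in the existing web questionnaire is convenient and keeps the topic out of the masked T1 and T2 interviews, but it is optional. The cost is a few self-report items per assessment and an edit to the table and one section. Nothing in the design, sample size or main analysis changes.
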